**Table GZEA.4. Prohibited Medications that Lower Heart Rate**

| Antihypertensive                                                                                                                                                                                                                                                               | Antiarrhythmic                                                                                                                                                                                                          | Psychoactive                                                                                                                                                                                                                                                                       | Other                                                                                                                                                                                            |
|--------------------------------------------------------------------------------------------------------------------------------------------------------------------------------------------------------------------------------------------------------------------------------|-------------------------------------------------------------------------------------------------------------------------------------------------------------------------------------------------------------------------|------------------------------------------------------------------------------------------------------------------------------------------------------------------------------------------------------------------------------------------------------------------------------------|--------------------------------------------------------------------------------------------------------------------------------------------------------------------------------------------------|
| 
 
• Beta-adrenergic receptor blockers (including beta-adrenergic blocking eye drops used for glaucoma)
 
• Clonidine
 
• Methyldopa
 
• Non-dihydropyridine calcium channel blockers
 
• Reserpine
 
 | 
 
• Adenosine
 
• Amiodarone
 
• Dronedarone
 
• Flecainide
 
• Procainamide
 
• Propafenone
 
• Quinidine
 
• Sotalol
 
 | 
 
• Donepezil
 
• Lithium
 
• Opioid analgesics
 
• Phenothiazine antiemetics and antipsychotics
 
• Phenytoin
 
• Selective serotonin reuptake inhibitors
 
• Tricyclic antidepressants
 
 | 
 
• Anesthetic drugs (propofol)
 
• Cannabis
 
• Digoxin
 
• Ivabradine
 
• Muscle relaxants (e.g., succinylcholine)
 
 |

### 6.3. Lifestyle and/or Dietary Requirements

Throughout the study, subjects may undergo medical assessments and review of compliance with requirements before continuing in the study.

#### 6.3.1. Meals and Dietary Restrictions

The CRU will provide subjects with standardized meals while resident at the CRU. While resident in the CRU, patients may not consume any food or caloric drinks other than that provided by the CRU. When not resident in the CRU, patients may resume their regular diet.

Subjects should fast (excluding water) for 8 hours prior to predose blood sampling, performing predose ECGs, and dose administration. Subjects should remain fasting (excluding water) for at least 4 hours postdose. Postdose ECG measurements should be taken at least 5 minutes prior to any food intake.

### **6.3.2. Caffeine, Alcohol, and Tobacco**

While confined at the CRU, subjects are required to adhere to the CRU smoking and caffeine policy during the inpatient treatment days. Subjects should otherwise not intentionally change their consumption of tobacco- or caffeine-containing products during the study.

No alcohol will be allowed during the 24 hours before and 72 hours postdose, and 24 hours before each CRU admission and each outpatient visit, and throughout the duration of each CRU visit. Between visits, daily alcohol consumption should not exceed 2 units for males and 1 unit for females (a unit is defined in Exclusion Criterion [34], Section 6.2).

### **6.3.3. Activity**

Subjects will refrain from strenuous exercise during the period of confinement at the CRU and will otherwise maintain their normal level of physical activity throughout the entire study (i.e., will not begin a new exercise program nor participate in any unusually strenuous physical exertion).

### **6.3.4. Contraceptive Requirements**

Male subjects (regardless of their fertility status) with nonpregnant female partners of childbearing potential must agree to either remain abstinent (if this is their preferred and usual lifestyle), or to use condoms as well as 1 additional highly effective (<1% failure rate) method of contraception (such as combination oral contraceptives, implanted contraceptives, or intrauterine devices) or effective method of contraception (such as diaphragms with spermicide or cervical sponges) from the time of first administration of the investigational product until the last study visit or 90 days following the last dose of investigational product, whichever is longer.

Men and their partners may choose to use a double-barrier method of contraception; however, barrier protection methods without concomitant use of a spermicide are not an effective or acceptable method of contraception (each barrier method must include use of a spermicide). The use of male and female condoms as a double-barrier method is not considered acceptable due to the high failure rate when these barrier methods are combined.

Male subjects with pregnant partners should use condoms during intercourse from the time of first administration of the investigational product until the last study visit or 90 days following the last dose of investigational product, whichever is longer. Male subjects should refrain from sperm donation from the time of first administration of the investigational product until the last study visit or 90 days following the last dose of investigational product, whichever is longer.

Male subjects who chose to remain abstinent (if this is their preferred and usual lifestyle) must adhere to the contraception requirements indicated above should their circumstances change.

Male subjects who are in exclusively same-sex relationships (as their preferred and usual lifestyle) are not required to use contraception.

#### **6.4. Screen Failures**

Subjects who do not qualify at screening due to a transient minor illness (such as a cold) may be rescreened 4 or more weeks after documented resolution of symptoms. Subjects who are taking any medication or medications specified in the Exclusion Criteria (Section 6.2) may be rescreened following a sufficient washout period determined by the investigator based on the exclusion criteria. Subjects who qualify at screening and Day -1 but are not dosed for the cohort may be rescreened for a future cohort. Subjects may be rescreened if they failed under previous inclusion and exclusion criteria that have been amended in the protocol, for example, TG or LDL values that would now be considered eligible under the current Inclusion Criterion [8] or [9]. When rescreening is performed, the individual must sign a new informed consent form (ICF) and will be assigned a new study identification number.

## 7. Treatment

### 7.1. Treatment Administered

The doses to be administered are presented in Section 5.1 and Table GZEA.5.

The investigational product will be administered either via an SC injection or as a slow IV infusion (over at least 30 minutes for Cohorts 1 and 2, or at least 60 minutes for Cohort 6). For SC administration, LY3475766 and placebo will be administered at a maximum volume of 2 mL per injection. A maximum of 6 injections may be necessary to achieve higher planned dose levels.

The drug product LY3475766 is supplied for clinical trial use as 75 mg of a lyophilized powder in a glass vial. Further dilution may be needed for IV administration. See Pharmacy Instructions for more information.

Placebo will be sterile saline (0.9% NaCl). Placebo doses should be held in the pharmacy for an equivalent amount of time as is required to prepare doses of LY3475766.

Investigative sites must have resuscitation equipment, emergency drugs, and appropriately trained staff available during the injection or infusion and for at least 6 hours after subjects have completed receiving their injections or infusions.

**Table GZEA.5. Treatments Administered Subcutaneously**

| Dose Level   | LY
Concentration
per Vial
(mg/mL) | Number of Vials | Volume
per
Injection
(mL) | Number of Injections | Total
Volume of
Injection
(mL) |
|--------------|--------------------------------------------|-----------------|------------------------------------|----------------------|-----------------------------------------|
| LY 100 mg/PL | 50                                         | 1.3             | 2.0                                | 1                    | 2                                       |
| LY 300 mg/PL | 50                                         | 5               | 2.0                                | 3                    | 6                                       |
| LY 600 mg/PL | 50                                         | 10              | 2.0                                | 6                    | 12                                      |

Abbreviations: LY = LY3475766; PL = placebo.

Injection site selected for SC administration should be the abdominal region approximately 5 cm from the umbilicus and the treatment has to be administered through the needle applied at approximately 45° with pinching of the skin. Because subjects may receive multiple injections per dose, each injection should be administered in a different abdominal quadrant in Cohorts 3 and 4 (rotating from right upper quadrant, to right lower quadrant, to left lower quadrant, to left upper quadrant), the quadrant used should be recorded at the time of the injection. For Cohort 5 where 6 SC injections are necessary, the injections should be administered into 6 separate regions of the abdomen: upper right, middle right (same level as umbilicus), lower right, lower left, middle left (same level as umbilicus), and upper left. Administering in a clockwise or counterclockwise direction should be considered to avoid injecting into the same location twice. The abdominal location for each injection should be recorded at the time of the injection. All injections should be performed within a total of 10 minutes. Subcutaneous administration of

LY3475766 should be done by a limited number of individuals for consistency. The same type of syringe and needle should be used for all subjects to ensure all injections are delivered to a consistent depth target into the SC space.

All clinical trial materials provided to the investigator will be stored in a secure place and dispensed by appropriately trained persons. The dispensing of the investigational product will be fully documented. Detailed records of the amounts of the investigational products received, dispensed, and remaining at the end of the study will be maintained.

The investigator or designee is responsible for

- explaining the correct use of the investigational product(s) to the subject
- verifying that instructions are followed properly
- maintaining accurate records of investigational product dispensing and collection, and
- returning all unused medications to Lilly or its designee at the end of the study.

**Note:** In some cases, sites may destroy the material if, during the investigative site selection, the evaluator has verified and documented that the site has appropriate facilities and written procedures to dispose of clinical materials.

### ***7.1.1. Packaging and Labeling***

LY3475766 will be provided to the investigative site as bulk supply in open-label vials by Lilly or its designee. Placebo will be provided to the investigative site as commercially available saline vials by Lilly or its designee.

Clinical trial materials will be labeled according to the country's regulatory requirements, and will be stored, inventoried, reconciled, and destroyed according to applicable regulations. Clinical trial materials are manufactured in accordance with current good manufacturing practices.

The investigational products will be labeled according to the country's regulatory requirements.

## **7.2. Method of Treatment Assignment**

Subjects who meet all criteria for enrollment will be randomized to 1 of the study treatment groups on Day 1. Subjects will be randomized in a 3:1 ratio to receive LY3475766 or placebo.

### ***7.2.1. Selection and Timing of Doses***

The actual time of all dose administrations will be recorded in the subject's electronic case report form (eCRF).

## **7.3. Blinding**

This is a double-blinded study; subjects and investigator site personnel will be blinded to treatment assignment (and to the results of postbaseline serum lipid levels) with the exception of the site staff preparing study drug.

Blinding will be maintained throughout the conduct of the study as described in the separate Blinding Plan. Emergency codes will be available to the investigator. A code, which reveals the treatment [group] for a specific study subject, may be opened during the study only if the subject's well-being requires knowledge of the subject's treatment assignment.

If a subject's study treatment assignment is unblinded, the subject must be discontinued from the investigational product, unless the investigator obtains specific approval from a Lilly clinical pharmacologist (CP) or clinical research physician (CRP) for the study participant to continue in the study. During the study, emergency unblinding should occur only by accessing the study subject's emergency code.

In case of an emergency, the investigator has the sole responsibility for determining if unblinding of a subject's treatment assignment is warranted for medical management of the event. The subject's safety must always be the first consideration in making such a determination. If the investigator decides that unblinding is warranted, it is the responsibility of the investigator to promptly document the decision and rationale and notify Lilly as soon as possible.

Upon completion of the study, all codes must be returned to Lilly or its designee.

#### **7.4. Dose Modification**

Any available PK data may be used to guide dose selection or to determine if the number of doses to be studied may be reduced in conjunction with known safety data. Safety data, in particular AEs, SAEs, and adverse laboratory abnormalities, will be independently assessed by the investigator and will be considered related to the investigational product unless there is clear evidence that the event is not related.

##### **7.4.1. Dose Escalation**

By nature of being a dose-escalation study, data will be evaluated on an ongoing basis until the highest planned dose has been administered or the MTD is determined. If the highest planned dose is not reached, the highest dose level that is tolerated will be designated as the MTD.

Safety data will be the primary criteria for the dose escalation. In addition, if available at the time of dose escalation decision, PK results (maximum observed drug concentration [ $C_{max}$ ], AUC, and total body clearance of drug calculated after IV administration) will be used as supporting data for dose escalation, but such data are not required. No dose decision can occur without prior discussion and agreement between the investigator and the Lilly CP.

After review of these data, an agreement on the appropriate dose will be made by the investigator and sponsor for the next cohort/dose level. The magnitude of dose escalations may be adjusted following data review, but subsequent escalations cannot be increased by more than approximately 3-fold (a half-log increment) in PK exposure or predicted AUC.

Dose-escalation decisions will primarily be based on available safety and tolerability data obtained up to Day 8 from Cohorts 1, 2, and 6 and up to Day 15 from Cohorts 3, 4, and 5 (Section 10.3.6). Additionally, any available PK data may be used to guide dose selection or to determine if the number of doses to be studied may be reduced.

If any of the following scenarios occur, dosing at the current level and further dose escalation will be interrupted until a further sponsor decision:

- 1) Three or more LY3475766-treated subjects develop AEs that are considered to be related to study treatment and graded as at least moderate, clinically significant, and not responsive to supportive care
- 2) One or more LY3475766-treated subject develops AEs that are considered to be related to study treatment and graded as severe
- 3) One or more LY3475766-treated subjects develop SAEs that are considered to be related to study treatment

In case any of the 3 scenarios above occurs at a given site (independently of treatment assignment since site investigators are blinded), this site is not allowed to continue dosing at the current level without written agreement from the sponsor.

In addition to safety reasons, the sponsor may decide to stop further dose escalation if pharmacodynamic data obtained from the previous cohorts are considered sufficient.

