**Figure GZEA.1. Dose escalation for Protocol J1T-MC-GZEA.**

Potential subjects will be screened to assess their eligibility to enter the study within 28 days prior to Day 1. In case of safety concerns, participants may be required to stay at the clinical site for a longer period at the discretion of the investigator. Subjects in all cohorts will return to the clinical research unit (CRU) as outpatients at predetermined visits for up to approximately 84 days postdose for follow-up assessments. In case a subject cannot come to the site for 1 or several outpatient visits, home visits may potentially be performed instead, depending on the circumstances and if agreed upon between investigator and sponsor.

Subjects will be confined at the CRU:

- from Day -1 (the day before dosing) to Day 4 (72 hours postdose) for IV cohorts (with outpatient visits starting on Day 8), and
- from Day -1 (the day before dosing) to Day 8 (168 hours postdose) for SC cohorts.

This is a randomized double-blinded SAD study in dyslipidemic but otherwise healthy male and female subjects investigating the safety, tolerability, PD, and PK of LY3475766 versus placebo.

Subjects will be enrolled in 6 cohorts:

- Cohort 1: 10 mg LY3475766 or placebo IV
- Cohort 2: 30 mg LY3475766 or placebo IV
- Cohort 3: 100 mg LY3475766 or placebo SC
- Cohort 4: 300 mg LY3475766 or placebo SC
- Cohort 5: 600 mg LY3475766 or placebo SC
- Cohort 6: 1000 mg LY3475766 or placebo IV

Safety and tolerability will be assessed throughout the study by means of vital sign measurements, safety laboratory tests, ECGs, physical examinations, automated office blood pressure monitoring (AOBPM), and AE recording. Sampling schedules, doses, and number of cohorts may be adjusted based on ongoing review of the PK, safety, and tolerability data. Additional follow-up visits may occur depending upon the PK and/or safety data.

Doses and the number of cohorts may be adjusted based on ongoing review of the PK, safety, and tolerability data at visits described in Section 2.

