## 5.4. Scientific Rationale for Study Design

A subject- and investigator-blinded, randomized, placebo-controlled design has been chosen to minimize bias in the primary objective of this study.

The study is intended to estimate a maximum tolerated dose (MTD) or establish that doses exceeding the expected therapeutic dose are tolerated. Safety, tolerability, PK, and preliminary PD data will assist in identifying an appropriate dose range for subsequent clinical studies.

While recently published European Medicines Agency guideline (EMA 2017) recommends use of sentinel dosing in first-in-human studies, it also allows for flexibility in a proposed dosing approach based on the available scientific data and preclinical assessment of a given molecule. The intended and exaggerated pharmacological responses of LY3475766 have been well characterized in multiple preclinical pharmacology models. Toxicology studies have suggested that non-monitorable or clinically unmanageable concerns would be unlikely to occur in humans treated with LY3475766. Based on the available data, LY3475766 does not present an uncertainty profile necessitating a sentinel dosing approach. Furthermore, sentinel dosing with low-risk compounds, such as LY3475766, may lead to inability to interpret data due to false-positive AE findings in the absence of data from all cohorts or placebo-treated subjects.

Dyslipidemic but otherwise healthy subjects have been chosen to evaluate preliminary PD parameters in a potentially responsive population. Utilizing this subject population mitigates possible confounding effects of comorbidities and concomitant medications. Therefore, this study will provide the most unbiased assessment of the safety and tolerability while allowing for assessment of PD parameters.

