## Revised Protocol Sections

**Note:** All deletions have been identified by ~~strikethroughs~~.  
All additions have been identified by the use of underscore.

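### Protocol Section 7.4.1 would name an MTD after a stop for sufficient PD data, with no tolerability limit observed

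*Combined protocol and SAP*

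**What the plan says.** Protocol Section 7.4.1 opens by recognising two ways for escalation to end: "data will be evaluated on an ongoing basis until the highest planned dose has been administered or the MTD is determined". It then gives the designation rule, without qualification: "If the highest planned dose is not reached, the highest dose level that is tolerated will be designated as the MTD". The planned top dose is in Section 5.1: "Cohort 6: 1000 mg LY3475766 or placebo IV".

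The closing paragraph of Section 7.4.1 adds a further way to end, set apart from safety grounds in its opening words: "the sponsor may decide to stop further dose escalation if pharmacodynamic data obtained from the previous cohorts are considered sufficient".

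Section 5.4 states the purpose as a pair of alternatives: "The study is intended to estimate a maximum tolerated dose (MTD) or establish that doses exceeding the expected therapeutic dose are tolerated".

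No other text narrows the designation. Appendix 1 of the protocol only expands the abbreviation MTD, and the SAP does not mention an MTD.

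**The concern.** An MTD is a statement about tolerability: higher doses were not tolerated, or were judged likely not to be. The designation sentence makes that statement follow from something else, namely that the top planned dose was not given. The two coincide only if intolerance is the sole reason to stop short, and the section itself provides another reason.

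After a PD stop, a dose with a clean safety record would therefore carry the same label as a dose beyond which escalation was halted for toxicity. Estimating an MTD is one of the two intents in Section 5.4, and the same section says that the study's data will help to identify a dose range for later trials. A label that reads as a safety ceiling when none was found would misstate the result on that intent.

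**Working it through.** **Side-by-side reading.** Apply Section 7.4.1 literally to three ways in which escalation can end:

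| How escalation ends | Tolerability limit seen? | Effect of the designation sentence |
|---|---|---|
| 1000 mg IV given and tolerated | No | Not triggered |
| Stopped short for safety or tolerability | Yes | Highest tolerated level is the MTD |
| Stopped short for sufficient PD data | No | Highest tolerated level is the MTD |

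The second and third rows get the same label from opposite evidence. The first and third rows have the same clean evidence, but only the third gets an MTD. The opening sentence of the section does not provide for the third row at all.

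**Where the option could act.** The amendment overview in Appendix 6 says that Cohort 4 has to be repeated because follow-up data were limited. Under the current protocol, escalation had thus already passed Cohorts 1 to 3. The remaining points at which a PD stop would fall short of the top dose are after Cohort 4 (300 mg SC) and after Cohort 5 (600 mg SC).

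**Illustration of the gap.** Inputs: SC bioavailability F of 50% to 80% (Section 5.1); SC doses of 300 and 600 mg; top dose of 1000 mg IV. Formula: IV-equivalent dose in AUC = SC dose × F, assuming AUC proportional to dose.

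- The protocol's own figure for 300 mg SC is reproduced: 300 × 0.5 = 150 mg and 300 × 0.8 = 240 mg. Gap to the top dose: 1000/240 = 4.2-fold to 1000/150 = 6.7-fold.
- For 600 mg SC: 600 × 0.5 = 300 mg and 600 × 0.8 = 480 mg. Gap: 1000/480 = 2.1-fold to 1000/300 = 3.3-fold.

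**Cross-check with the protocol's projections.** Table GZEA.2 gives an AUC of 1324.9 µg·h/mL for 10 mg IV, or 132.5 per mg. Table GZEA.3 gives 9911.0 for 100 mg SC, or 99.1 per mg. The ratio is 99.1/132.5 = 0.75, so 600 mg SC is about 600 × 0.75 = 450 mg IV and the gap is 1000/450 = 2.2-fold. This treats the multiple-dose SC figure as comparable with the single-dose IV figure, which the documents do not establish.

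**The case against.** **The instructions do not strictly collide.** A PD stop and the designation sentence can both be carried out as written. Section 5.4 offers an alternative to an MTD, and a PD stop could be placed under it. This stands in part: the defect is a rule that yields the wrong label, not two orders that cannot both be obeyed. But Section 7.4.1 never sends a PD stop to that alternative, and its designation is mandatory.

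**Dropping a cohort might redefine the highest planned dose**, so that the sentence is never triggered. Section 5.1 does allow doses and the number of cohorts to change, but on PK, safety and tolerability data. PD is not among the grounds.

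**The consequence is small.** The MTD is not an objective or endpoint in Table GZEA.1, the SAP plans no MTD output, and a reader of the results would see the adverse events beside the label. This stands, and it limits the weight of the point. It does not make the label right.

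Four stronger readings are tempting, and the documents do not support them:

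- *That amendment (d) introduced the PD stop.* The sentence is reprinted under the revised Section 7.4.1 in Appendix 6, where "All additions have been identified by the use of underscore". That marking cannot be seen on this sentence in the text available, the appendix also reprints unchanged wording, and the overview does not mention a PD stop. The point does not depend on when the sentence was added.
- *That PK data open an equal route.* Section 7.4.1 lets PK data be used "to determine if the number of doses to be studied may be reduced", but Section 7.4 couples this with known safety data. Fewer doses need not mean stopping below the top one, and a PK-based cut may simply change the planned doses under Section 5.1.
- *That any of the first five cohorts could be so labelled.* Escalation had already moved past Cohorts 1 to 3. In any case Section 5.5 puts 10 mg at about half the MABEL, which is itself projected to lower TG by less than 10%, so a stop there for sufficient PD data was never plausible.
- *That the label would pass into the Investigator's Brochure.* Nothing in the documents says so.

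**Conclusion.** The concern holds for the PD stop. As written, Section 7.4.1 would designate a well-tolerated dose as the MTD if the sponsor ended escalation after Cohort 4 or 5 because the PD data were sufficient. No text in the protocol or SAP prevents this.

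The size is that of a wrong conclusion on one stated intent, conditional on an optional sponsor decision. Estimation, safety monitoring and the planned analyses are untouched. The 2.1- to 3.3-fold gap for 600 mg SC shows how far such an MTD could lie below the planned top exposure. It is an illustration only: it rests on a generic bioavailability range and on dose-proportional AUC, and the protocol's own projections point to the lower end, about 2.2-fold. It does not measure error in any result.

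**What to change.** Reconcile the passages of Section 7.4.1 with each other and with Section 5.4:

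- Make the MTD designation apply only when escalation ends for safety or tolerability.
- Record the reason for stopping when the escalation decision is made.
- For any other stop short of the planned top dose, state *MTD not determined; highest dose studied and tolerated = X*. That outcome can then be reported under the second intent in Section 5.4.

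The cost is one revised protocol sentence, one item in the escalation record and matching wording in the study report. The SAP needs no change, since it has no MTD output. No dose, threshold or stopping rule is proposed or altered.
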